### Compliance

Compliance with consumption will be monitored every other day through phone interviews which will be followed by face-to-face interviews once a week. Participants will be asked to consume one capsule before lunch and one capsule before dinner; this will also increase their compliance with consumption. All participants will be requested to bring back their first bottle at the end of the primer intervention and then they will be given the second bottle of supplements. If the remaining capsules of every participant will exceed 10% of the total administered supplements (12 capsules), the participant will be categorized as non-adherent. All individuals, including those who will complete the study or those who will not complete for any reasons, will follow the same schedule.

### Sample size

On the basis of sample size formula suggested for a balanced, crossover designed trials (Fig. 3), considering the non-inferiority margin of δ = 0.05 (clinically meaningful difference), with an expected true difference of 0.02 between the means, and a population variance of 0.01 and considering the significance level of α = 0.05, the sample size to achieve 80% power is calculated to be 35. The final sample size was increased to 40 to accommodate the expected 10% of dropout rate.

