To assess the effects of oral *N. sativa* oil on the gene expression of TNF-α, PPAR-γ, and adiponectin along with the changes in serum concentrations of these factors among obese and overweight women.To conduct a crossover, placebo-controlled, randomized clinical trial (RCT), to compare the altered gene expression as well as other outcome measures of every individual with herself, as her own control, and with the control group to achieve more accurate results.To investigate the alterations in serum levels of liver enzymes including alanine transaminase (ALT), aspartate transaminase (AST), and alkaline phosphatase (ALP) as well as measuring lipid profile including total cholesterol, triglyceride, high density of lipoprotein cholesterol (HDL-C), low density of lipoprotein cholesterol (LDL-C), and atherogenic indices before and after every intervention period.

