### Statistical analysis

All statistical analyses will be performed with the Statistical Package for the Social Sciences (SPSS) (IBM SPSS Statistics for Windows, version 23.0; IBM Corp.), with significance set at *P* < 0.05. Normality of data will be assessed using the Shapiro–Wilk test. The values of continuous variables will be presented as means ± SEM. Categorical data will be presented as number and percentage in study groups. The general linear model repeated measure procedure will be incorporated to compare the quantitative outcome variables between the intervention periods in crude and multivariable adjusted models taking the rolling method and participants’ age, baseline values as between-person factors, and the change in physical activity level, energy intake, and body weight as covariates. The criterion for statistical significance will be defined as *P* < 0.05. Pearson’s correlation coefficient will be applied to show the correlation between biochemical measures and anthropometric indices.

We will analyze the results with intention to treat (ITT) and without participants with non-compliance (study completers). ITT analysis is based on the initial treatment assignment and not on the treatment eventually received. In the ITT method, participant-loss associated bias as well as misallocation or non-adherence of participants is near completely limited. In the case that researchers observe a significant difference between those allocated to receive an intervention and those who actually received that intervention (and adhere to it), per-protocol analysis, which is an additional analysis adjusted for actual treatment, will be performed. The results of the two mentioned analyses will be compared with each other.

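### The 80% power comes from a non-inferiority calculation, but the trial plans a test of difference from placebo, so the stated power is not that of the planned test

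*Protocol article*

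**What the plan says.** The Sample size section sets out the calculation by "considering the non-inferiority margin of δ = 0.05 (clinically meaningful difference), with an expected true difference of 0.02 between the means", with "a population variance of 0.01", and "considering the significance level of α = 0.05". It concludes that "the sample size to achieve 80% power is calculated to be 35", raised to 40 for 10% dropout. The formula is in Fig. 3, which is not shown. Its legend defines δ as the clinically meaningful difference and lists the expected true difference as a separate term.

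The first objective in the Background is to assess the effects of oral N. sativa oil on expression and serum levels of three markers. The second is to compare each woman with herself and "with the control group to achieve more accurate results". The Study design section describes a placebo-controlled crossover trial. Under Statistical analysis, "The general linear model repeated measure procedure will be incorporated to compare the quantitative outcome variables between the intervention periods", with significance at P < 0.05. The margin of 0.05 is not mentioned again as a criterion for any conclusion.

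**The concern.** A non-inferiority calculation gives the chance of showing that N. sativa is not worse than placebo by more than the margin. The trial asks whether N. sativa changes the markers relative to placebo, and non-inferiority to paraffin oil would not answer that. The distance powered for, 0.03, is neither the expected difference (0.02) nor the clinically meaningful one (0.05). A test of difference would use one of those two.

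The same 0.05 also serves as both a tolerable loss and an effect worth finding, two different quantities. What is at stake is how the result is read. A non-significant comparison would be taken as coming from a trial with 80% power, although that figure was never computed for the comparison made.

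**Working it through.** **Inputs (Sample size section).** δ = 0.05; expected difference 0.02; variance 0.01; alpha 0.05, sidedness not stated; power 80%; stated n = 35; final size 40. With 10% dropout, 40 × 0.9 = 36 evaluable.

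**Step 1: reproduce 35.** The usual crossover non-inferiority form, with the variance of the estimated difference equal to σ²/(2n), is

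n = (z₁₋α + z₀.₈₀)² × σ² / [2 × (δ − difference)²].

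- One-sided alpha 0.05: (1.645 + 0.8416)² × 0.01 / (2 × 0.03²) = 34.35, rounded up to 35. This matches.
- z = 1.96 in the same formula: 43.6, so 44.
- Equivalence by two one-sided tests: 47.6, so 48.
- Expected difference in the favourable direction (distance 0.07), one-sided: 6.3, so 7.
- No factor 2 in the denominator, one-sided: 68.7, so 69.

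Of these variants only the first gives 35. One-sided alpha is thus a back-calculation, not a statement in the text. The 0.03 distance also implies that the expected 0.02 lies towards inferiority, against the trial's rationale. Dropout follows: 35/0.9 = 38.9, so 39, made even at 40.

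**Step 2: power of the planned test, same variance term.** With n as the total number of women, σ²/(2n) corresponds to a within-woman difference with variance 0.01/2 = 0.005. For 36 women, SE = √(0.005/36) = 0.01179. Two-sided alpha 0.05 is assumed; power is from the noncentral t with 34 degrees of freedom.

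- Difference 0.02: 0.02/0.01179 = 1.70, power 37.8%.
- Difference 0.05: 0.05/0.01179 = 4.24, power 98.5%.

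Under this term the protocol's own one-sided non-inferiority test has 80.2% power at 36 women, which confirms that the term is the one behind the stated 80%.

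**Step 3: the other readings of the variance.** If 0.01 is the variance of the within-woman difference, SE = √(0.01/36) = 0.01667.

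- Difference 0.02: ratio 1.20, power 21.5%.
- Difference 0.05: ratio 3.00, power 83.0%.

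On this reading the factor 2 makes 35 a per-sequence number (70 in total), and 36 women would give the non-inferiority test itself only about 55% power. If the variance of the difference were 0.02, power would be 13% at 0.02 and 54% at 0.05.

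**Step 4: size for a superiority test, step 1 variance term, two-sided 0.05, 80% power (normal approximation).**

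- For 0.02: 7.849 × 0.01 / (2 × 0.02²) = 98.1, so 99.
- For 0.05: 7.849 × 0.01 / (2 × 0.05²) = 15.7, so 16.

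A one-sided superiority test at 0.05 for a difference of 0.02 would need 77.3, so 78. The mismatch does not depend on assuming two-sided testing.

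**The case against.** The best defence is that the protocol calls 0.05, not 0.02, clinically meaningful. For 0.05 the planned test has about 98% power under the formula's own variance term, and about 83% if 0.01 is the variance of the difference. Low power at 0.02 then concerns an effect below what the protocol itself considers relevant. This stands, and it limits the point. A reader might infer that the trial is simply underpowered. The documents do not support that: the answer depends on which difference is sought and on what the variance describes.

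A reader might also take 21% power, and the corresponding requirement of about 196 women (7.849 × 0.01 / 0.02²), as the size of the error. Those figures treat 0.01 as the variance of the within-woman difference, which the protocol never says, and they drop the factor 2 needed to reproduce 35. They mix the wrong-hypothesis problem with a separate question, whether 35 is a total or per sequence. With the variance term held fixed, the figures are 38% and about 99 women.

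Finally, the formula is not visible and neither section states sidedness. The inference rests on the legend and the match at 35. That is good evidence, but it should be labelled as inference. None of this removes the mismatch: the text itself names a non-inferiority margin, and no part of the analysis uses one.

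**Conclusion.** The point holds as a mismatch between the hypothesis sized for and the hypothesis tested. The stated 80% is not the power of the planned comparison. With 36 evaluable women, the variance term that reproduces 35 and two-sided alpha 0.05, power is about 38% at 0.02 and 98% at 0.05. If 0.01 is the variance of the within-woman difference, it is about 21% and 83%. Three assumptions carry these figures: the formula inferred for Fig. 3, two-sided testing, and the meaning of the variance. The mismatch itself needs none of them. An unconditional finding of inadequate power is not supported.

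**What to change.** Rewrite the Sample size paragraph for the fixed size of 40 (36 evaluable):

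- Keep the inputs used (0.05, 0.02, 0.01, alpha 0.05, 80%) on record as the basis for 40, and state openly that they formed a non-inferiority calculation.
- Replace the 80% claim with a two-sided superiority power statement for one named primary outcome, with its unit.
- Say what the variance of 0.01 refers to. The documents do not supply a standard deviation of the difference, so the sponsor must define it before a single power figure is written.
- Give power at both 0.02 and 0.05: about 38% and 98% under the formula's variance term, or about 21% and 83% if 0.01 is the variance of the within-woman difference.

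The cost is one paragraph. The Trial status section reports initial recruitment as complete, and no extra enrolment or change to data collection is asked for. The downside is a less favourable stated power at the expected difference.

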**Fig. 2 Fig2:**
[figure not shown]
SPIRIT figure: Template of the content for the schedule of enrolment, interventions, and assessments

**Fig. 3 Fig3:**
[figure not shown]
Formula for calculating sample size in crossover studies. δ is the clinically meaningful difference, μ2–μ1 is an expected true difference between the means, σ^2^ is the population variance, α is the significance level, and *β* is the power of the test

### Intervention

Before the study initiation, two trained researchers will introduce the study to participants. Participants, who will decide whether to join the investigation, will be asked to sign informed consent forms. The questionnaires will be reviewed and approved by the ethical committee of Shahid Sadoughi University of Medical Sciences. Data will be gathered by one of the main investigators. Individuals in the intervention group will receive two capsules of *N. sativa* (produced by Barij Essence Pharmaceutical Co.) and individuals in the placebo group will receive two capsules of paraffin oil per day. Both *N. sativa* and placebo capsules and the packs will be identical in terms of appearance, weight, texture, size, and smell and will only be differentiated by a code name (“A” or “B”). A person who is not involved in this project will label the containers “A” or “B.” Every capsule of *N. sativa* includes 1000 mg of *N. sativa* oil, which will consist of 0.01 mg of Thymoquinone-active component. The gas chromatography–mass spectrometry (GC/MS) test of every 50 g of *N. sativa* powder is presented in Table 1.

**Table 1 Tab1:** Fatty acid content in every 50 g of *N. sativa* (GC/MS^a^ test)

Test	Reference method	Acceptable value	Result
Appearance	Visual	Brown color	Brown color
Odor	Organoleptic	Specific	Specific
Palmitic acid (%)	WR10^b^	11–14	11.84
Stearic acid (%)	WR10	–	2.00
Oleic acid (%)	WR10	17–26	22.14
Linoleic acid (%)	WR10	52067	59.66
Linolenic acid (%)	WR10	–	1.79
Thymoquinone (%)	EP^c^ 0.8 (2.2.23)	–	0.54

^a^Gas chromatography–mass spectrometry

^b^Rectangular waveguide size

^c^European Pharmacopoeia

### Matching energy intakes between groups

With regard to the dietary energy intakes of participants, we decided to give every individual an iso-energy dietary program in order to match every participant based on their energy and macronutrient intakes. Hence, an eight-week one-to-one individualized iso-energy dietary program for every intervention period, based on every participant’s current weight, will be performed. After determination of required energy, the registered dietician will develop a plan of servings from each food group that will fulfill the macronutrient distribution. The required participants’ daily energy intake will be distributed as follows: < 30% from fat (mainly mono-unsaturated and poly-unsaturated fatty acids); 55% from carbohydrates; and 1.2–1.5 g protein per kg of body weight. After baseline measurements, each participant will meet the registered dietitian three times during each intervention period (at weeks 0, 4, and 8).

Dietary intake will be quantified using three-day food records, including one weekend day and two weekdays as well as 24-h food recalls. Daily macro- and micro-nutrient intakes will be calculated by analyzing food data using nutritionist IV software (First Databank, San Bruno, CA, USA) modified for Iranian foods.

Shahid Sadoughi University of Medical Sciences will be responsible for any related problems; adverse events will be reported to the medical ethics committee from the initiation of the study. Participants may withdraw from the study for any reason at any time.

General information including age, diseases, medications, and supplements will be recorded through interviews at the beginning of the study. Physical activity level will be calculated through a questionnaire using metabolic equivalents (METs) at the beginning and at the end of every intervention period. Results of the assessments will be shared for every participant separately.

Primary outcomes consist of gene expression and serum concentration levels of adiponectin, PPAR-γ, and TNF-α. Secondary outcome measures consist of blood levels of lipid profiles and anthropometric measurements. The assessments of the outcomes are listed below.

### Gene expression assay

A total of 2 mL of fresh blood will be transferred into a tube consisting of ethylenediaminetetraacetic acid (EDTA); immediately after, peripheral blood mononuclear cells (PBMCs) will be isolated using density centrifugation with Ficoll-Paque [32]. Total mRNA will then be extracted using a related RNA kit [33]. Total extracted RNA will be then reverse transcribed to complementary DNA (cDNA) using a cDNA synthesis kit [34]. The mRNA gene expression of adiponectin, PPAR-γ, and TNF-α will be applied using the real-time polymerase chain reaction (PCR) method, after designing primers. The housekeeping gene will be glyceraldehyde phosphate dehydrogenase (GAPDH) in real-time PCR assessments.

### Biochemical measurements

A total of 12 mL fasting blood sample of venous blood will be collected from every participant. Circulating adiponectin and TNF-α will be assessed by enzyme-linked immunosorbent assay (ELISA). Blood pressure will be measured with a well-validated automated digital blood pressure monitor (Beurer, Germany, BM 85), following American Heart Association guidelines. Biochemical analyses including total cholesterol, triglycerides, HDL-C, LDL-C as well as liver enzymes, including ALT, AST, and ALP, will be measured using automated enzymatic methods. The values of atherogenic factors, including the ratios of HDL-C/LDL-C and LDL-C/HDL-C, will be calculated. All laboratory data will be identified by an ID number to maintain the participants’ confidentiality.

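### The only two atherogenic indices named, HDL-C/LDL-C and LDL-C/HDL-C, are reciprocals: one measurement tested twice, with answers that can differ if both are analysed untransformed

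*Protocol article*

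**What the plan says.** The objectives at the end of the protocol's Background include changes in liver enzymes and lipids "and atherogenic indices before and after every intervention period". That text does not say which indices are meant. The only place that does is Biochemical measurements, where atherogenic factors, "including the ratios of HDL-C/LDL-C and LDL-C/HDL-C, will be calculated". No other index is named in the article.

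Under Statistical analysis, "The values of continuous variables will be presented as means ± SEM", and for comparisons "The general linear model repeated measure procedure will be incorporated to compare the quantitative outcome variables between the intervention periods". The threshold is P < 0.05, with no distinction between outcomes. Normality is to be checked with the Shapiro–Wilk test, but the text names no transformation and does not say what follows a failed check. It does not say which of the two ratios carries the conclusion.

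On the standing of these variables, the outcome paragraph says: "Secondary outcome measures consist of blood levels of lipid profiles and anthropometric measurements". The ratios are not listed there by name.

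**The concern.** Two outcomes are listed where there is one. Reporting a ratio and its inverse would be harmless if the two always gave the same answer, but on the arithmetic scale they need not. The mean of LDL-C/HDL-C is driven by women whose ratio is high, and the mean of HDL-C/LDL-C by women whose ratio is low. If the two kinds of women respond differently, or merely vary by chance in different directions, the two means can disagree about whether the index improved.

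The answer to this part of the third objective may then depend on which way up the ratio is written. Testing both at 0.05 gives two chances of a positive result on one quantity. It also leaves the choice of which to emphasise open until the results are known.

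**Working it through.** The plan gives no figure for these indices, so there is nothing to reproduce. The check has three steps.

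**1. Algebra.** Let R = LDL-C/HDL-C. Then HDL-C/LDL-C = 1/R, and the product of the two is 1 for each woman at each visit. For a small change in log R, the change in R is about R × Δlog R, and the change in 1/R is about −(1/R) × Δlog R. The same individual changes are therefore averaged with opposite weights.

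**2. A counterexample (invented values).** Two women have R = 2.0 and 4.0 on placebo, and 1.5 and 4.8 on active treatment.

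- Mean R: (2.0 + 4.0)/2 = 3.00 becomes (1.5 + 4.8)/2 = 3.15, which is worse.
- Mean 1/R: (0.5 + 0.25)/2 = 0.375 becomes (0.6667 + 0.2083)/2 = 0.4375, which is better.
- Geometric mean change in R: √[(1.5/2.0) × (4.8/4.0)] = √(0.75 × 1.20) = √0.90 = 0.949. For 1/R it is 1/0.949 = 1.054. These are the same statement, so the log scale gives one answer.

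**3. How often it would matter.** The simulation used 20,000 paired trials per setting, with a paired t-test as a simple stand-in for the repeated-measures model.

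- From the protocol: 35 participants (Sample size: "the sample size to achieve 80% power is calculated to be 35"), taken here as 35 pairs, and the 0.05 level.
- Assumed, not in the protocol: lognormal R with median 2.5, between-person log-SD 0.3 to 0.4, within-person log-SD 0.10 to 0.20, and a true effect of 0, −0.02 or −0.05 on the log scale (reductions of about 0, 2 and 5%).

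| True effect (log) | Between SD | Within SD | Opposite clinical direction | Exactly one test significant | At least one significant |
|---|---|---|---|---|---|
| 0 | 0.3 | 0.10 | 18.7% | 4.6% | 7.0% |
| 0 | 0.3 | 0.20 | 20.0% | 5.1% | 7.4% |
| 0 | 0.4 | 0.15 | 24.2% | 6.1% | 7.9% |
| −0.02 | 0.3 | 0.10 | 13.3% | 8.4% | 16.1% |
| −0.02 | 0.3 | 0.20 | 18.2% | 6.0% | 9.3% |
| −0.02 | 0.4 | 0.15 | 21.4% | 8.0% | 11.9% |
| −0.05 | 0.3 | 0.10 | 2.5% | 18.1% | 58.2% |
| −0.05 | 0.3 | 0.20 | 11.5% | 11.2% | 21.8% |
| −0.05 | 0.4 | 0.15 | 10.0% | 17.4% | 32.8% |

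A second run over the same ranges gave 19 to 25% opposite directions with no effect, and up to 22% of trials with exactly one significant test under a 2 to 5% effect. In no simulated trial were both tests significant in opposite directions.

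**The case against.** Four points can be made on the other side.

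- **The list is open.** The protocol introduces the two ratios with a word that allows others, and a journal article need not list every derived variable. This stands. A reader might infer that total cholesterol and triglycerides are wasted because they enter no named index. The protocol does not support that: both are measured, both appear in the third objective in their own right, and both belong to the lipid profile, which is a secondary outcome. What remains open to criticism is the redundancy of the pair that is named.
- **The analysis scale is partly inferred.** Means ± SEM is a presentation format, and a failed Shapiro–Wilk check might lead to a transformation set out in an analysis plan that is not shown. This stands as a condition: if both ratios are log-transformed, the conflict disappears. But the text states none, so an untransformed analysis is the fair default reading. A normality check applied to each ratio separately could also lead to a different treatment of each.
- **The size is modest.** The two-woman example is extreme by construction, and the variances are assumed. A reader might infer that the report could show significant benefit on one ratio and significant harm on the other. The simulation gives no support for that. The disagreement is in point estimates, mainly when the effect is near zero, or in one test reaching significance and the other not.
- **The stakes are low.** No primary outcome, sample-size figure or safety decision rests on these ratios. This stands.

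**Conclusion.** The point holds as a small one. That the two named indices are one measurement is certain. That they can give different answers is also certain if both are analysed untransformed, which is how the plan reads but is not stated outright. The frequencies rest on the assumed lognormal variances, on 35 pairs and on a paired t-test. Under those assumptions with no true effect, roughly 19 to 25% of trials show opposite directions, and the chance of at least one false positive is about 7 to 8% instead of 5%. With a 2 to 5% effect, about 6 to 22% of trials would have one ratio significant and the other not. This affects only how one part of the third objective is reported, at secondary level or below.

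**What to change.** Before unblinding, add about one sentence to Biochemical measurements or Statistical analysis. It should designate one ratio, for example LDL-C/HDL-C with lower values as better, and state that its logarithm will be analysed and the result reported as a ratio of geometric means. The inverse should not be tested separately. If wanted for readers, it follows by inverting the estimate and its confidence limits.

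An additional index built from total cholesterol or triglycerides, both already measured, is optional and does not follow from this point.

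The change needs no new samples, assays or visits. Although the Trial status section says initial recruitment is complete, this is a choice of calculation and analysis and can still be made. Fixing it before the allocation is known prevents the choice of ratio from depending on the results.
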